| Glasgow Coma Scale (GCS) score at admission, per unit                                   |                  |         |                   |         | 0.90 (0.85–0.96)   | <0.0001 |
| Serum creatinine concentration at Day 0 (per 1 mg/dL)                                   | 1.46 (1.24–1.71) | <0.0001 |                   |         | 1.43 (1.23–1.66)   | <0.0001 |

The variance inflation factor value was less than 2 in all cases. OR=odds ratio.

 Model for sub-phenotype A2 among patients with A phenotype. AUROC (95% CI) of the model: 0.86 (0.82–0.91). The optimal threshold was 0.19, yielding a sensitivity of 76.0% and specificity of 82.0%. The positive predictive value (PPV) was 50.0%, the negative predictive value (NPV) was 93.5%, and the overall accuracy was 80.8%.

 Model for sub-phenotype B2 among patients with B phenotype. AUROC (95% CI) of the model: 0.88 (0.83–0.92). The optimal threshold was 0.10, yielding a sensitivity of 82.7% and specificity of 85.9%. The positive predictive value (PPV) was 47.0%, the negative predictive value (NPV) was 97.1%, and the overall accuracy was 85.5%.

 Model for sub-phenotype C2 among patients with C phenotype. AUROC (95% CI) of the model: 0.89 (0.87–0.91). The optimal threshold was 0.52, yielding a sensitivity of 88.6% and specificity of 75.2%. The positive predictive value (PPV) was 86.0%, the negative predictive value (NPV) was 79.3%, and the overall accuracy was 83.7%.

**Table S7. Distribution of the phenotypes identified in the cluster analysis in the INSTINCT cohort based on the portal of entry.**

| Phenotype identified in cluster analysis | Portal of entry       |                   |                   |
|------------------------------------------|-----------------------|-------------------|-------------------|
|                                          | Skin and soft tissues | Vascular catheter | Other or unknown  |
| Ac (n=355)                               | 286 (80·5)     | 24 (6·8)          | 45 (12·7)         |
| Bc (n=432)                               | 1 (0·2)               | 431 (99·8) | 0                 |
| Cc (n=430)                               | 18 (4·2)              | 3 (0·7)           | 409 (95·1) |

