## 7. Primary objective.

To determine retrospectively whether different clinical phenotypes exist among patients (adults and children) who develop *Staphylococcus aureus* bacteremia.

Secondary objectives:

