### Secondary objectives:

- 1 To evaluate the reproducibility of these clinical phenotypes and their correlation with mortality (30 days and 6 months)
- 2 To derive and validate a simplified probabilistic model of phenotype assignment.
- 3 External validation of the simplified probabilistic model of clinical phenotype assignment in a prospective cohort, and determination of associations with mortality and the development of complicated bacteremia within 6 months.
- 4 To apply microbiological (clonality testing, genome sequencing), biochemical and immunological techniques to elucidate the pathophysiological and genetic mechanisms underlying the phenotypes.

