## **8. Data analysis.**

ISAC Cohort: Objectives 1 and 2: Missing value analysis and imputation, if applicable, will be performed using standard techniques. To derive the phenotypes, a two-step cluster analysis with silhouette analysis will be performed on a randomly selected subcohort including two-thirds of the patients. The phenotypes will be represented as chord diagrams and heat maps. The distribution of phenotypes and characteristics will be validated on the other subcohort with one-third of the patients. Multivariate analysis (Cox or logistic regression) will be performed to control for the effects of antibiotic treatment and control of focus of infection on the association between the identified phenotypes and the outcome variable. Objective 3: A binary (if two phenotypes are obtained) or multinomial (if >2) logistic regression model will be used to predict the phenotypes obtained. A simplified probabilistic model of phenotype assignment will then be developed based on the final logistic regression model selected.

Prospective cohort: (Objective 4). Each patient with SAB will be assigned a phenotype that will be calculated on the basis of the simplified probabilistic model. Mortality rates (at 30 days and six months), persistent bacteremia and complicated bacteremia will be compared between the different types of phenotypes. Multivariate analyses (Cox or logistic regression) will be calculated to control for the effect of other covariates

(such as treatment administered or source control) on the association between identified phenotypes and outcome variables.

Study of genetic, immunological, biochemical and microbiological variables in representative patients with different phenotypes, randomly selected from the prospective cohort of HUVVM and HUVV cases (Objective 5):

Differences in frequencies or medians of the data for genetic virulence factors, biomarkers or immunological factors across the different phenotypes will be analyzed by the chi-square or Mann-Whitney U test and multivariate logistic regression models, taking into account possible confounding variables.

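### The external validation of the phenotype assignment model has no reference phenotype, and no stated rule lets the clustering conclude that there are no phenotypes

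*Combined protocol and SAP*

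**What the plan says.** The third secondary objective is "External validation of the simplified probabilistic model of clinical phenotype assignment in a prospective cohort, and determination of associations with mortality" and complicated bacteremia. Methods section 8 (Data analysis) calls the same work Objective 4; its Objective 3 is the derivation of the model. For the prospective cohort that section states "Each patient with SAB will be assigned a phenotype that will be calculated on the basis of the simplified probabilistic model". It then compares mortality, persistent bacteremia and complicated bacteremia between the assigned groups, with Cox or logistic adjustment.

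The primary objective reads "To determine retrospectively whether different clinical phenotypes exist among patients (adults and children) who develop" *S. aureus* bacteremia. For ISAC, "a two-step cluster analysis with silhouette analysis will be performed on a randomly selected subcohort including two-thirds of the patients", and the remaining third is used to check the distribution of phenotypes and their characteristics. The next step is "A binary (if two phenotypes are obtained) or multinomial (if >2) logistic regression model will be used to predict the phenotypes obtained".

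The supplementary appendix reports model performance in the Table S6 footnotes. For sub-phenotype A2 it says "The positive predictive value (PPV) was 50.0%, the negative predictive value (NPV) was 93.5%, and the overall accuracy was 80.8" (per cent).

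**The concern.** External validation of a classifier needs something to compare its output with. Here the model under test supplies the only label in the prospective cohort, and the planned analysis relates that label to outcome. This answers the second half of the objective (association) and leaves the first half (validity of assignment) untouched. The second secondary objective has a similar gap: it promises to derive and validate the model in ISAC, but section 8 describes only its derivation.

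An outcome difference cannot stand in for the missing check. Table S6 shows creatinine in models A and C, oxygen saturation in B and C, and age and Glasgow score in C. Some of these may predict death whichever cluster the patient belongs to, so a model that misassigns many patients could still separate survival curves.

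The primary objective has a related weakness. It asks whether phenotypes exist, but the plan describes no finding that would count as none.

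Misassignment would also carry into the mechanistic substudy. That substudy samples patients by model-assigned phenotype and expects 25 to 33 per group.

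**Working it through.** **1. Table S6 reproduced.** Inputs are the stated sensitivity and specificity and the group sizes in Tables S3 to S5. PPV = TP/(TP+FP).

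- A2 (88 v 370): TP = 0.760 × 88 = 66.9; FP = 0.180 × 370 = 66.6; PPV = 50.1% (stated 50.0%).
- B2 (75 v 498): TP = 0.827 × 75 = 62.0; FP = 0.141 × 498 = 70.2; PPV = 46.9% (stated 47.0%).
- C2 (694 v 403): TP = 0.886 × 694 = 614.9; FP = 0.248 × 403 = 99.9; PPV = 86.0% (as stated).

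Negative predictive values and accuracies also reproduce. Accuracy needs a benchmark: calling every A patient A1 is right in 370/458 = 80.8%, the same as model A. Calling every B patient B1 is right in 498/573 = 86.9%, against 85.5% for model B. Model C (83.7%) clearly beats its benchmark of 694/1,097 = 63.3%.

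**2. What the appendix checks, and where.**

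- Table S6: models against cluster labels, in the derivation cohort.
- Table S7: clusters against portal of entry in INSTINCT. Agreement is (286 + 431 + 409)/1,217 = 92.5%, kappa 0.89. It does not test the sub-phenotype models and is not the prospective cohort.
- Tables S10 and S11: mortality by sub-phenotype, with the label taken from the predictive model.

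None compares a model-assigned sub-phenotype with an independent label outside the derivation cohort.

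**3. Can the association be null?** Yes. Take 1,000 patients, mortality of 20–40% (the protocol's literature review), and an assumed group share of 25–50% and two-sided 5% level. Schoenfeld's power is Φ(√(d·p(1−p))·|ln HR| − 1.96). With 200 events and a 25% share, √(200 × 0.1875) = 6.12; with 400 events and a 50% share, √(400 × 0.25) = 10. Power is then 70–98% for HR 1.5 and 20–45% for HR 1.2. In Table S10 the lower limit for A2 is 1.01.

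**4. Number of clusters.** Mean silhouette is undefined for one cluster. As an illustration, 40 data sets of 1,800 patients were simulated with no clusters (12 Gaussian variables, 1,200/600 split). K-means stood in for two-step clustering, and nearest-centroid assignment for the logistic model.

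| | Independent variables | One severity gradient (loading 0.6) |
|---|---|---|
| k chosen by silhouette (2–5) | 2 in 40/40 | 2 in 40/40 |
| Mean silhouette | 0.06 | 0.21 |
| k chosen by BIC (1–5) | 1 in 40/40 | 3 in 35, 4 in 5 |
| Hold-out adjusted Rand index, mean | 0.05 | 0.91 |

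With the severity gradient, and mortality made to depend on it, the groups differed in mortality at the 5% level in 40/40 runs although no clusters existed. When mortality was unrelated, about 5% of runs were significant.

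**5. Is a check feasible at the planned size?** The half-width is 1.96·√(p(1−p)/n). For 80% agreement in 1,000 patients it is ±2.5 points. For 80% sensitivity in 250–333 patients per phenotype it is ±5.0 to ±4.3 points. Small sub-phenotypes would be less precise. If the ISAC share of A2 (88/458 = 19.2%) held among the 283 A patients in Table S9, there would be about 54, giving ±10.7 points.

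**The case against.** A reader might infer that neither objective can come out negative. The documents do not support that. The association half of the third secondary objective can fail, as step 3 shows.

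A reader might also infer that the clustering is bound to find phenotypes. That is not established. Two-step clustering can return one cluster if an information criterion that scores one cluster sets the number, and the plan does not say that silhouette sets it. The defect is an unspecified rule. Nor would a random hold-out reproduce any arbitrary cut: with independent variables agreement was 0.05, so the hold-out could expose failure. What is missing is a criterion that makes such a failure count.

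The reported performance is not uniformly weak. The threshold-free AUROCs are 0.86, 0.88 and 0.89. C2 makes up 694 of the 857 sub-phenotype 2 patients, and pooled PPV is 743.8/980.6 = 76%. At the A/B/C level, Table S7 is a real external check of clusters against portal of entry. The absence of optimism correction can be stated only for these documents; the main report is not among them.

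All of this stands and narrows the point. It does not supply a reference label for the sub-phenotypes in the prospective cohort.

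**Conclusion.** The concern holds in a limited form. Followed as written, the plan tests whether model-assigned groups differ in outcome. It does not test whether the model assigns patients correctly, although the objective names that validation. The likely size of the problem is shown by ISAC itself: about half of those labelled A2 or B2, and 14% of those labelled C2, are not in that cluster. External figures could be better or worse. That a positive association is weak evidence of correct assignment rests on the assumption that some inputs act on mortality directly; this is plausible but not shown in these documents.

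On the primary objective, the conclusion is that no decision rule is stated: no branch for one cluster, no criterion for their number and no failure condition. The simulation is illustrative only, because the method and variables were stand-ins and the documents give no observed silhouette.

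**What to change.** 1. **Reference label.** Freeze the ISAC cluster solution. In the held-out third and the prospective cohort, assign each patient to a cluster from the clustering variables available in both cohorts. Report the assignment model against that label: kappa, sensitivity and PPV per phenotype, and calibration. Show mortality under both labels. Bootstrap-correct the ISAC performance, repeating variable selection and threshold choice in each resample.
2. **Number of clusters.** Include one cluster as a candidate through a criterion that can score it, for example BIC within the two-step procedure. Report stability in the hold-out or by leaving out one ISAC hospital at a time (there are 11). Any cut-off is for the sponsor to fix in advance. This makes a negative result possible, but step 4 shows that neither BIC nor hold-out agreement separates clusters from a severity gradient when the criterion ignores correlation within clusters. The report should say so, or use a criterion that allows for it.
3. **Numbering.** Use one numbering for the objectives in the objectives list and in section 8.

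No new patients are needed. The cost is more analysis work; reported accuracy may fall and fewer clusters may be supported. The reference label would be limited to shared variables: Table S9 shows no temperature, heart rate, inotrope or hemodialysis rows, which Tables S3 to S5 have. It would also depend on imputation, since Table S2 shows up to 33.2% missing in ISAC (bilirubin).

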**Table S11. Multivariate Cox regression of 30-day mortality for each of the identified phenotypes in the FEN-AUREUS cohort**

| VARIABLE                     | A                |       | B                |       | C                |        |
|------------------------------|------------------|-------|------------------|-------|------------------|--------|
|                              | aHR (95%CI)      | p     | aHR (95%CI)      | p     | aHR (95%CI)      | p      |
| Source control within 3 days | 0.46 (0.20–1.08) | 0.07  | 0.57 (0.35–0.93) | 0.02  | 0.41 (0.13–1.32) | 0.13   |
| Sub-phenotype 2              | 2.02 (1.25–3.29) | 0.004 | 2.11 (1.30–3.44) | 0.002 | 2.44 (1.47–4.06) | 0.0006 |
| ID team visit                | 0.43 (0.25–0.74) | 0.002 | 0.66 (0.40–1.10) | 0.10  | 0.59 (0.38–0.90) | 0.02   |

 Sub-phenotype 2 within each phenotype, based on the probable portal of entry, was identified using the single predictive model assigned to each phenotype according to the probable portal of entry.

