### Secondary Objectives

- 1 To evaluate the reproducibility of the clinical phenotypes and their correlation with mortality (30 days and 6 months).
- 2 To derive and validate a simplified probabilistic model of clinical phenotype assignment.
- 3 External validation of the simplified probabilistic model of clinical phenotype assignment in a prospective cohort and determination of associations with mortality and the development of complicated bacteremia within 6 months.
- 4 To apply microbiological (clonality testing, genome sequencing), biochemical and immunological techniques to elucidate the pathophysiological and genetic mechanisms underlying the phenotypes.

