## 5. Expected sample size and basis for determination.

For the retrospective study (objectives 1-3) based on the ISAC database: we estimate that we will be able to analyze at least 1,800 cases of SAB that meet the inclusion criteria. For objective 4: we estimate prospective inclusion of 1000 cases from the 14 participating centers during 34 months of follow-up.

For objective 5: we estimate that 3 or 4 phenotypes will be identified, and therefore that 100 patients/isolate will be sufficient to provide 25-33 patients per phenotype, which will allow a reasonable number of cases for comparison of microbiological, genetic, endothelial and immunological parameters.

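### The ISAC mortality model appears to use cluster labels and the prospective model uses labels from the simplified model, so the two hazard ratios are not like for like

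*Combined protocol and SAP*

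**What the plan says.** Methods section 8 (Data analysis) takes the ISAC steps in this order.

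1. The labels come from clustering: "To derive the phenotypes, a two-step cluster analysis with silhouette analysis will be performed on a randomly selected subcohort including two-thirds of the patients". The remaining third is used to validate the distribution of phenotypes and characteristics.
2. A Cox or logistic model then adjusts for antibiotic treatment and source control when estimating effects "on the association between the identified phenotypes and the outcome variable".
3. Only after that, under what section 8 calls Objective 3, is a regression built to predict the phenotypes and reduced to a simplified assignment model.

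For the prospective cohort the exposure comes from that last step: "Each patient with SAB will be assigned a phenotype that will be calculated on the basis of the simplified probabilistic model". The mortality models there are again described as concerning identified phenotypes, so one phrase covers both kinds of label.

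The objectives tie the two analyses together. Secondary Objective 1 is "To evaluate the reproducibility of the clinical phenotypes and their correlation with mortality (30 days and 6 months"; Secondary Objective 3 is "External validation of the simplified probabilistic model of clinical phenotype assignment in a prospective cohort and determination of associations with mortality".

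The appendix shows the same pattern. The footnotes to Tables S10 and S11 say that sub-phenotype 2 in INSTINCT and FEN-AUREUS "was identified using the single predictive model assigned to each phenotype according to the probable portal of entry". Table S6 gives the agreement of those models with the cluster labels in ISAC; for A2, "The positive predictive value (PPV) was 50.0%, the negative predictive value (NPV) was 93.5"%.

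**The concern.** A patient's cluster label and model-assigned label need not agree. If the ISAC HR belongs to one and the prospective HR to the other, the validation HR has no matching derivation value.

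A lower HR in the prospective cohort could mean that the phenotypes did not carry over, or only that the label changed. An HR that is not lower could mean that they did carry over, or that the inputs to the assignment model predict death in their own right. The plan has no analysis that separates these readings. It does not apply the model label to ISAC mortality, re-cluster the prospective cohort, or correct for misclassification. What is at stake is any numerical comparison of the ISAC result under Secondary Objective 1 with the external result under Secondary Objective 3.

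**Working it through.** **Inputs.** Cluster sizes in ISAC: A1/A2 370/88 (Table S3), B1/B2 498/75 (Table S4), C1/C2 403/694 (Table S5). Sensitivity and specificity of each assignment model against the cluster label, from the Table S6 footnotes: A 76.0% and 82.0%, B 82.7% and 85.9%, C 88.6% and 75.2%.

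**Step 1: reproduce Table S6.** With n2 and n1 the cluster sizes, TP = sens × n2, FP = (1 − spec) × n1, TN = spec × n1 and FN = (1 − sens) × n2. Then PPV = TP/(TP + FP), NPV = TN/(TN + FN) and accuracy = (TP + TN)/N.

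- A: TP 66.9, FP 66.6, TN 303.4, FN 21.1. PPV 50.1%, NPV 93.5%, accuracy 80.8% (table: 50.0, 93.5, 80.8).
- B: TP 62.0, FP 70.2, TN 427.8, FN 13.0. PPV 46.9%, NPV 97.1%, accuracy 85.5% (table: 47.0, 97.1, 85.5).
- C: TP 614.9, FP 99.9, TN 303.1, FN 79.1. PPV 86.0%, NPV 79.3%, accuracy 83.7% (table: 86.0, 79.3, 83.7).

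The table reproduces within rounding. Over 458 + 573 + 1,097 = 2,128 patients, weighted accuracy is 83.6%, so about 16% change label. The share called sub-phenotype 2 moves from 19.2% to 29.1% (A), 13.1% to 23.1% (B) and 63.3% to 65.2% (C). Because the figures follow from the full ISAC counts, they look like in-sample performance; error in a new cohort could be larger.

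**Step 2: illustrate the effect on the HR.** Assume that death depends on the cluster label only and that label error is unrelated to death. The 30-day risk in sub-phenotype 1, r1, is not in the documents, so take 10–25%. The ISAC cluster-label HR is not given either, so try 2, 3 and 4.

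- r2 = 1 − (1 − r1)^HR
- risk if assigned 2 = PPV × r2 + (1 − PPV) × r1
- risk if assigned 1 = (1 − NPV) × r2 + NPV × r1
- HR under assigned labels = ln(1 − risk if assigned 2) / ln(1 − risk if assigned 1)

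Example, A with r1 = 0.15 and HR = 3: r2 = 1 − 0.85³ = 0.386. Assigned 2: 0.501 × 0.386 + 0.499 × 0.15 = 0.268. Assigned 1: 0.065 × 0.386 + 0.935 × 0.15 = 0.165. HR = ln(0.732)/ln(0.835) = 1.73.

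| Cluster-label HR | A | B | C |
|---|---|---|---|
| 2.0 | 1.39–1.40 | 1.40–1.42 | 1.55 |
| 3.0 | 1.69–1.74 | 1.72–1.79 | 1.95–1.99 |
| 4.0 | 1.93–2.04 | 1.98–2.13 | 2.27–2.35 |

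Ranges are over r1 of 10–25%. At HR 3.0 about half of the log HR is kept in A and B, and 61–62% in C.

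**Step 3: test the assumption against the reported results.** Run the same formulas backwards with the ISAC class mix. The INSTINCT adjusted HR for B, 3.40 (Table S10), would need a cluster-label HR of about 9 at r1 = 10% and about 11 at r1 = 15%. At r1 = 20% it cannot be reached: even with r2 = 1 the formula gives at most 3.38. The confidence interval is wide (2.02–5.72), so this proves nothing. It does suggest that error unrelated to death may not be the whole story. The Table S6 models contain age, Glasgow score, creatinine and oxygen saturation, which could predict death directly. In that case the shift is smaller than in the table above, or goes the other way.

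**The case against.** The strongest reply is that the change of label is deliberate. Secondary Objective 3 is about the simplified model, and the label that can be assigned to a new patient is the right exposure for it. Secondary Objective 1 asks a different question of the clusters. This stands: neither analysis is wrong in itself, and the gap matters only when the two HRs are set side by side.

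Three further points have force. That the ISAC exposure is the cluster label is inferred from the order of section 8, and the ISAC mortality HRs are not in these documents. The A2, B2 and C2 models come from the reported results; the protocol text plans one binary or multinomial model and names no sub-phenotypes. At the main-phenotype level, Table S7 shows INSTINCT cluster labels agreeing with portal of entry in 286 + 431 + 409 = 1,126 of 1,217 patients (92.5%), so structure was looked at separately there. Table S7 does not reach the sub-phenotypes to which Tables S10 and S11 apply.

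A reader might infer something stronger: that a faithful replication would look like a failed one. The documents do not support that. Under the illustration the HR shrinks but stays above 1. The plan sets no criterion that the prospective HR must equal the ISAC one. All six model-assigned HRs in Tables S10 and S11 lie between 1.93 and 3.40 with intervals excluding 1.

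**Conclusion.** The point holds in limited form. As section 8 is written, the ISAC and prospective mortality HRs describe different exposures, and no planned analysis bridges them. The labels differ materially for A2 and B2, where about half of those assigned are not in the cluster, and less so for C2.

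The effect on the HR cannot be sized from the documents. A fall from 3.0 to about 1.7–2.0 is conditional on death depending only on the cluster label, on Table S6 accuracy carrying over, and on an assumed baseline risk of 10–25%. The first assumption is doubtful given the models' inputs, and the direction of the shift is therefore open. The six favourable external HRs show that the assigned label is prognostic; alone they do not show that the clusters' own association with death was reproduced. This is a worthwhile improvement to the plan and does not invalidate the study.

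**What to change.** Add to the ISAC part of section 8: once the simplified model and its cut-offs are fixed, repeat the 30-day mortality model with the same covariates and the model-assigned label as exposure, in the held-out third or with cross-validated assignment. Report this HR beside the cluster-label HR, and name it as the derivation value for comparison with the INSTINCT and FEN-AUREUS HRs. Use separate terms for clustered and assigned phenotypes throughout.

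The covariate sets should also match when HRs are compared: Table S11 includes the infectious-disease team visit and Table S10 does not.

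The cost is one extra model on existing data and a sentence or two of text, with no new patients or data. The downside is that the benchmark HR may be less favourable than the cluster-label one.

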Study of dysregulated cytokine production: Blood samples from 100 patients will be tested to determine differences between the phenotypes for the main markers of cytokine dysregulation. Cytokine and adhesion molecule levels will be determined by Bio-Plex assay. EDTA tubes will be used for the collected samples. Blood samples will be centrifuged for 15 min at 1000 g, aliquoted into 0.2 mL tubes, and stored at -80°C until analysis. For each sample, the Bio-Plex multiplex immunoassay will be used to simultaneously quantify (working in microplates) up to 12 human cytokines. The cytokines to be analyzed will be chosen from among the following: basic FGF, eotaxin, G-CSF, GM-CSF, IFN- $\gamma$ , IL-1 $\beta$ , IL-1ra, IL-1 $\alpha$ , IL-2R $\alpha$ , IL-3, IL-12 (p40), IL-16, IL-2, IL-4, IL-5, IL-6, IL-7, IL-8, IL-9, GRO- $\alpha$ , HGF, IFN- $\alpha$ 2, LIF, MCP-3, IL-10, IL-12 (p70), IL-13, IL-15, IL-17A, IP-10, MCP-1 (MCAF), MIG,  $\beta$ -NGF, SCF, SCGF- $\beta$ , and SDF-1 $\alpha$ .

Study of markers of endothelial dysfunction: Differences in the main markers of endothelial dysfunction (plasma levels of E-selectin, VCAM-1 and ICAM-1) in the 100 representative samples. For determination of adhesion molecule levels, EDTA and heparin plasma samples (for measurement of E-selectin) will be collected and centrifuged within 30 minutes of blood collection. Subsequent aliquots will be stored at -80°C until analysis: E-selectin, VCAM-1 and ICAM-1 levels will be assessed with commercially available ELISA kits and a photometer (Tecan Sunrise, Craisheim, Germany) measured at 450 nm.

Immunological study: quantification of immunosuppression by flow cytometry: Whole blood drawn into K3-EDTA collection tubes will be used for flow cytometry analysis (BD FACS Canto II) of different subpopulations. For analysis of the main lymphocyte subpopulations (LT, LB, NK, CD4, CD8), a 6-color antibody panel (for CD45, CD3, CD4, CD8, CD16+56, CD19) will be used, and for Treg lymphocytes, a 3-color antibody panel (CD4, CD25 and CD127). Analyses of activated CD4 and CD8 lymphocytes: OX40+, HLA-DR+, CD28, inhibited lymphocytes (PD-1, CTLA-4), and myeloid-derived suppressor cells (MDSC) with simultaneous

labelling of CD45, CD33, CD11b, HLA-DR, CD14 and CD15. Dendritic cells: Lin- CD45 + CD11c- CD11b + CD123 + HLA-ABChigh HLA-DRhigh CCR7high OX40L + DC-SIGN + CD86highCD80highCD40highCD83+.

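### Objective 5 compares 3 or 4 phenotypes with a two-group rank test and sets no comparison scheme or error control across a wide marker panel

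*Combined protocol and SAP*

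**What the plan says.** Methods section 8 (Data analysis), in its paragraph on Objective 5, covers "Differences in frequencies or medians of the data for genetic virulence factors, biomarkers or immunological factors" and says that these differences "across the different phenotypes will be analyzed by the chi-square or Mann-Whitney U test and multivariate logistic regression models", allowing for possible confounders. The objective lists number the same work as secondary objective 4.

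Methods section 5 sets the group sizes: "we estimate that 3 or 4 phenotypes will be identified, and therefore that 100 patients/isolate will be sufficient to provide 25-33 patients per phenotype". Its only justification is qualitative: "which will allow a reasonable number of cases for comparison". Section 11 of the protocol summary says the same.

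The panel is described under Microbiological studies and Other methods:
- cytokines: the assay will "simultaneously quantify (working in microplates) up to 12 human cytokines", chosen from a list of 36 (my count), with no rule for when or how they are chosen;
- endothelial markers: three (E-selectin, VCAM-1, ICAM-1);
- flow cytometry: about 13 readouts by my count (five main lymphocyte subsets, Treg, OX40, HLA-DR, CD28, PD-1, CTLA-4, MDSC, dendritic cells);
- susceptibilities: 16 agents;
- virulence and resistance genes, and host gene variants: numbers not stated.

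For Objective 5 the documents give no alpha, primary marker, pairwise scheme or multiplicity rule, and they do not call the work exploratory.

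**The concern.** A two-group rank test cannot compare medians across three or four phenotypes in one step. An analyst following the text has to run it pair by pair, choose a reference group, or merge phenotypes, and the plan does not say which. Uncorrected pairwise testing raises the error rate within each marker. The breadth of the panel then raises it across markers.

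The substudy is meant to explain the mechanisms behind the phenotypes, and the literature review presents it as a route to new treatment strategies. Without a stated scheme, a reader of the results cannot tell a real marker difference from one that the number of tests would produce by chance.

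**Working it through.** **Inputs from the documents.** 100 patients; 3 or 4 phenotypes; 12 cytokines at most and 3 endothelial markers (15 soluble markers). Adding about 13 flow readouts gives 28, and 16 susceptibilities give 44.

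**Assumptions.** Two-sided 0.05 per test (none is stated), every null hypothesis true, and a between-marker correlation of 0 to 0.6.

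**The plan's own figure.** 100/4 = 25 and 100/3 = 33.3, so 25-33 per phenotype is reproduced. There is no power figure to reproduce.

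**Error within one marker.** Three groups give 3 pairs and four groups give 6. Pairs share groups, so their tests are dependent and the rate has to be simulated. Under the null:

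| Groups | Any pairwise Mann-Whitney p<0.05 | Kruskal-Wallis p<0.05 |
|---|---|---|
| 3 x 33 | about 12% (11.7-12.5% across runs) | about 5% |
| 4 x 25 | about 19-20% | about 5% |

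**Expected false positives, 15 markers, all pairs.** 15 x 3 x 0.05 = 2.25 and 15 x 6 x 0.05 = 4.5. These expectations hold whatever the correlation.

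**Chance of at least one false positive, 15 markers, all pairs.** The per-marker rate is carried across independent markers:
- 3 groups: 1 - 0.883^15 = 84% to 1 - 0.875^15 = 87%; direct simulation gave 86%.
- 4 groups: 1 - 0.805^15 = 96%; direct simulation gave 96%.
- At correlation 0.6, simulation gave 62% (3 groups) and 81% (4 groups).

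**One global test per marker, independent markers.** 1 - 0.95^15 = 54%; 1 - 0.95^28 = 76%; 1 - 0.95^44 = 90%. At correlation 0.6 the simulated values for 15 to 44 markers are about 34-52%. A global test therefore repairs the error within a marker but not the error across markers.

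**All pairs, 28 markers.** Simulated at correlation 0 / 0.3 / 0.6: 98% / 91% / 77% (3 groups) and 99.9% / 99% / 89% (4 groups).

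**Price of correction.** Difference detectable with 80% power, two-sample t-test, 25 per group, 27 markers (15 soluble plus an assumed 12 cell subsets; 28 markers give the same second figure to two decimals):
- alpha 0.05: 0.81 SD;
- alpha 0.05/27 = 0.00185 (one pair per marker): 1.18 SD;
- alpha 0.05/(27 x 6) = 0.00031 (six pairs per marker): 1.35 SD.

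**The case against.** The plan never says that all pairs will be tested. Mann-Whitney U may be shorthand for a rank-based comparison, and a multiplicity rule is often left out of a small mechanistic substudy. That is fair as far as it goes: the pairwise figures describe one way of carrying out the text, and alpha and marker correlation are assumptions. But Mann-Whitney U is the only rank test named, the sample size rests on 3 or 4 groups, and even one global test per marker leaves 54% for 15 independent markers. The core point stands.

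A reader might infer more than the documents support:
- **That false positives are near certain.** This needs all pairs tested on about 28 or more largely independent markers. The calculation 1 - 0.95^45 = 90% and 1 - 0.95^90 = 99% for 15 markers treats pairs that share groups as independent and is too high.
- **That chi-square is also the wrong test.** It compares any number of groups. A 10% trait has expected counts of only 2.5-3.3 per group, but for 5-10% traits the simulated size is about 3.2-4.4% at a nominal 5%, which is mildly conservative.
- **That groups of 25-33 cause the false positives.** Type I error does not arise from group size here. Small groups cost power and limit covariate adjustment.
- **That the section contradicts itself on regression.** The phrase "binary (if two phenotypes are obtained) or multinomial (if >2) logistic regression model" belongs to Objective 3, where phenotype is the outcome. For Objective 5, a logistic model of a binary marker with phenotype as a multi-level covariate would be legitimate. The model is under-specified, not wrong.

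**Conclusion.** The concern holds in limited form. The named rank test does not fit a comparison of 3 or 4 groups, and nothing in the plan controls error within or across markers. With uncorrected pairwise tests at 0.05, each marker carries a false-positive rate of about 12% or 19-20% instead of about 5%. Across the panel at least one false positive is likely rather than certain; how likely depends on the testing scheme, the number of markers and their correlation. The unstated numbers of genes and host variants could push it higher.

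The reach is limited to the mechanistic substudy of about 100 patients at two centres. Phenotype derivation, phenotype assignment and the mortality analyses do not depend on these tests.

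**What to change.** Amend the Objective 5 paragraph of Methods section 8:
1. Replace Mann-Whitney U with one Kruskal-Wallis test per continuous marker across all phenotypes, and state the alpha.
2. Keep chi-square for categorical traits; an exact test is optional where expected counts are small.
3. Run pairwise tests only where the global test is positive, with a named adjustment (Holm-adjusted Dunn tests would do).
4. Apply Benjamini-Hochberg false-discovery control across the markers. Other schemes are acceptable if fixed in advance.
5. State whether phenotype is the outcome or a covariate in the regression models.
6. Fix the cytokines before any result is linked to phenotype.

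This is analysis wording only, with no new patients or samples. The cost is fewer nominal hits and less power. The Bonferroni figures of 1.18 SD and 1.35 SD, against 0.81 SD uncorrected, show the scale at 25 per group; the loss under false-discovery control is smaller.
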